## Introduction

### Background

The decision about the need of an individual to require hospital admission relies on the assessment of patients’ symptoms, signs, past medical history, medication use, diagnosis, social support at home [1-3], and a judgment about the severity of illness based on estimated risk of deterioration in the subsequent hours and days [4].

Abnormalities of vital signs are quantified by comparison with normal measurements on healthy individuals recorded during periods of physiological stability. Within these individuals, the normal measurements vary and are influenced by age, sex, body composition, medication use, and physical condition [5-7]. There is a relation between the size of change from a physiologically normal range and the number of vital signs affected by abnormality and the frequency of adverse events [8]. Abnormality might be scored with generic tools that can be applied to the majority of patients, such as the National Early Warning Score [9], or tools that are disease-specific, such as the CURB65 [10], Blatchford [11], and DECAF (Dyspnea, Eosinopenia Consolidation, Acidemia, and Atrial Fibrillation) [12]. However, these scores can under- or overestimate risk in individual patients [13].

Knowing the values of an individual patient’s vital signs while well might help clinicians to better understand and interpret their changes or trends [14], their relative degree of deviation from the patient’s own normal and get a better estimate of their personal severity of illness. Similarly, mobility has been suggested to be a vital sign [15] and could be easily quantified by step counts. Normal mobility has been shown to be a protective factor [15]. Therefore, the assessment and comparison of step count during illness might be of value.

The general public are increasingly using devices such as smartwatches and mobile telephones that can potentially measure and record vital signs such as heart rate, heart rhythm, and oxygen saturation. Currently, approximately 90% of the population in the United States [16] and 94% in the United Kingdom [17] are smartphone users. Vital signs are also increasingly being recorded at home using conventional sphygmomanometers and pulse oximeters, and these values, if recorded, might also be available.

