**Secondary study end points**
Secondary end points will focus on four areas of interest:The difference between the heart rate at rest from the wearable device 24 hours, 1 week, and 1 month before assessment by emergency practitioners compared with the first set of vital sign parameters measured on admission to acute care.The change in daily steps taken in the month before admission to acute care.To describe the population that is wearing devices that collect data on vital signs in terms of gender, age group, severity of illness as measured by a standard set of vital signs, level of education, and digital literacy and frailty.To explore the association of changes in heart rate from the community to assessment in acute care services with clinical end points such as admission to a general ward or admission to a critical care area or discharge home within 24 hours from the time of clinical assessment.

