Data items were collected as part of the "Feasibility of Using resting heart rate and step counts from patient-held Sensors during clinical assessment of medical Emergencies" (FUSE) study.Site ID is the unique number for each site.Participant ID is a consecutive number (no identifiable information is collected).Location is the location where the patient is included in the study (ie, emergency department, medical admissions unit, ambulatory emergency care, or other).Sex as reported by the patient (ie, men, women nonbinary, or unknown).Date of birth, which will be used to compute an age category.Date and time of first presentation, defined as the time that a patient presents at the location.Highest level of education is the patient finished highest level of education or the level of education the patient is currently following (ie, primary school, secondary school, and higher education).Digital literacy is assessed using 2 questions asking for confidence of using the internet and confidence of using mobile apps, which patients can answer using a 5-point Likert scale.Device is the device used to measure heart rate, and the brand and type will be recorded.Phone is the phone that patients use, and this will be used to retrieve the step count and heart rate data. The brand and type will be recorded.Heart rate on the device is the heart rate that is stored and measured by the device, and the resting heart rate (as presented by the device), the minimum, maximum, and mean or median (depending on the device) will be retrieved on three-time points, namely on presentation, within 24 hours before presentation and within 1 week (plus or minus 1 day) before presentation.Walking distance is the number of steps of exact distance (in kilometers or miles), either measured by the device of the phone. The daily walking distance of the 7 days before the presentation will be recorded.Frailty as quantified through the Clinical Frailty Scale [19].Mobility will be assessed as either normal or impaired. Mobility is considered impaired if the patient is unable to get onto the bed unaided, either from the ambulance gurney or whichever way they arrive.Date and time of the first set of vital signs is defined as the time that the first set of vital signs are measured.Heart rate on admission is the first heart rate measured during clinical examination.National Early Warning Score [9] as a standardized assessment of the severity of illness, based on the first full measurements of respiratory rate (per minute), oxygen saturation (in %), temperature (in °C), heart rate (per minute), systolic blood pressure (in mm Hg), AVPU (alert, verbal, pain, and unresponsive) score, and the use of any supplemental oxygen.Outcome is assessed at midday on the day after the initial assessment and can be (ie, discharged, admitted to hospital, admitted to high care or intensive care, or deceased).

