#### Data Analysis

Data will be analyzed using SPSS (version 28; IBM Statistics). All variables will be assessed for normality. This study will use basic epidemiological data to determine if patient-owned monitoring devices can be used in an emergency care setting to assess the patient’s current severity of illness and compare it with their usual state of health.

Continuous data will be analyzed using the unpaired *t* test (if the data are normally distributed) or the Wilcoxon rank sum test (if the data are not normally distributed). Changes between measurements will be described as percentage change from the first measurement taken at home before admission as the assumed baseline and as an absolute change. Categorical data will be analyzed using chi-square test. Basic statistics and descriptives will be used to identify the distribution of patient and device characteristics. Missing data will not be imputed.

Associations between the baseline measurements and the specified clinical end points and the absolute and proportional change of physiological measurements and the specified clinical end points will be assessed using linear regression and logistic regression.

Patient characteristics will be expressed as absolute numbers per (sub)category for the total patient population, the discharged patients, and the admitted patients. The heart rate and step count data will be compared for their respective average or median for the different time points. Both will be tested for significant interaction between time, disposition, and change in either heart rate or step count using a generalized linear model.

For secondary exploratory analyses, the correlation between potential outcomes will be tested using Pearson coefficient correlation analysis (*r*), where the following interpretation will be used: below 0.10 negligible, between 0.10 and 0.39 weakly correlated, between 0.40 and 0.69 moderately correlated, between 0.70 and 0.89 strongly correlated, and above 0.89 very strongly correlated. The percentile change in heart rate and step count will be calculated in comparison to the baseline, which will be assumed to be at 30 days before a hospital visit.

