#### Secondary Outcome Measures

Secondary outcomes measures include measures of epidemiology and physiology:

We will report trends for heart rate and step count, specifically the difference between the heart rate at home 24 hours, 1 week, and 1 month before clinical assessment from the wearable device compared with the first vital signs measured on admission to acute care as both an absolute and a proportional change.

We will also describe the degree of association between changes to vital signs from the community to assessment in acute care services with admission to a general ward or admission to a critical care area or discharge home within 24 hours from the time of the first hospital assessment.

The population wearing or carrying devices will be described in terms of gender, age, ethnicity, level of education, and digital literacy and contrasted with data from national surveys.

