### Limitations

The distribution of wearables in the population might point toward the exclusion of a significant proportion of the population from this type of support: patients who are less financially well off or not sufficiently digitally or health literate might be disadvantaged in a future health care. This data will hence be collected as part of FUSE. While this study focuses on readily available data and will require in future supplementation by detailed qualitative data.

The study is conducted by a group of secondary care clinicians with expertise in medical emergencies. Many of the patients who will be screened and included will have previously presented in primary care. There is no theoretical reason that the results from this study might not be applicable to those presenting in primary care, but this might require future research.

In preparation of the study, we reviewed sales for the top 20 devices in the Dutch and British markets. For these devices, we have created a data dictionary for investigators that will enable them to assist patients in the location of relevant data. With new devices coming online and changes in consumer habits, the frequency distribution of these devices might however be soon outdated.

The study will explicitly not address the quality of data collected in wearables. We will, however, report on the distribution of devices and approval for medical use where applicable. In the same vein, we anticipate that the duration of usage by individuals will affect the measurements. This is something that we might not be able to evaluate in the current setup.

Given that patients will use a range of devices with different methods for data acquisition and different usage patterns our analysis will focus on the comparison of relative changes in parameters for individuals (intraindividual variation). This relies on the assumption that individuals will have a pattern of usage that is constant over time. Further research will be required, especially if it turns out that the variation between the collected parameters turns out to be large in the days before deterioration and presentation to the hospital.

Finally, future health care needs to be equitable. FUSE will include data that will allow us to gauge some aspects of equity, diversity, and inclusion which are crucial for the development of policy and strategy in this field.

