### Conclusions

This article describes a feasibility study. The results should aid power calculations and the design of more definitive observational and ultimately interventional trials.

From a health policy point of view, there is concern that, at present, device ownership might be more common in those who are younger and well off, thus potentially amplifying problems around equitable access to health care and emphasizing the inverse care law. The FUSE study and subsequent research should provide data that might direct manufacturers toward the design of devices that are suitable for the widest range of users. We hope that FUSE will help policymakers and clinical teams in the design of better and safer services around digitally enabled patients and for those who are not (yet) connected to mHealth systems.

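### The models relating heart-rate change to disposition name no age term; if age affects both the change and admission, the association could be masked, reversed or exaggerated

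*Protocol article*

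**What the plan says.** Under Data Analysis, associations between "the absolute and proportional change of physiological measurements and the specified clinical end points will be assessed using linear regression and logistic regression". No covariate or stratification factor is named. The same section then compares heart rate and step count over time: "Both will be tested for significant interaction between time, disposition, and change in either heart rate or step count using a generalized linear model". This is the only model whose terms are listed, and age is not among them.

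Age is available. The data items under Study Procedures include "Date of birth, which will be used to compute an age category", and the Clinical Frailty Scale is recorded too. Their stated use is descriptive. Under Secondary Outcome Measures, "The population wearing or carrying devices will be described in terms of gender, age, ethnicity, level of education, and digital literacy"; frailty joins that description under Secondary study end points; and Data Analysis tabulates patient characteristics overall and by discharged or admitted.

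The Background says of healthy individuals that "the normal measurements vary and are influenced by age, sex, body composition, medication use, and physical condition". The Conclusions expect that "device ownership might be more common in those who are younger and well off". The association itself is one of the secondary end points: "To explore the association of changes in heart rate from the community to assessment in acute care services with clinical end points".

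**The concern.** The study uses each patient as their own reference. For an absolute change, this removes an age effect that only shifts the resting level. It does not remove an age effect on how far heart rate moves during an acute illness. The percentage change, also planned, is less well protected. Its denominator is the baseline, so if age shifts the baseline, age enters the predictor even when the absolute rise is the same at every age.

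If age also affects the chance of admission, a model without age mixes the two effects. Suppose older patients rise less and are admitted more. Small rises are then concentrated among those most often admitted, and the association is weakened or reversed. If older patients rise more, it is inflated.

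This bears on how the result will be read. The Discussion (Anticipated Findings) foresees using change, or its absence, to support decisions about admission or care in the community. A crude association cannot show whether change carries information beyond what age already tells.

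**Working it through.** **The plan's own figures.** The only planned size is 40 hospitals × 50 patients = 2000 screened, which reproduces as a product. No alpha, power, effect size or SD is given for the association. The Results section reports 1137 screened, 452 included and 209 with at least two collection points (209/452 = 46.2%; 209/1137 = 18.4%). I use 209 as the analysable number. The article does not say that all 209 have paired heart-rate values, so this may be generous.

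**Assumptions, none from the documents.** Half the patients are older (p = 0.5). The within-age SD of change is σ = 15 bpm. Older patients' mean rise is smaller by d bpm (negative d means larger). The odds ratio of older age for admission is 4 or 6. About 40% to 49% are admitted.

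**Approximation by hand.** Per 10 bpm,

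log(crude OR) ≈ log(true OR) − log(age OR) × 10·d·p(1−p) / [σ² + d²·p(1−p)].

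- d = 10: the multiplier is 10 × 10 × 0.25 / (225 + 25) = 0.10.
  - True OR 1.20, age OR 4: 0.182 − 1.386 × 0.10 = 0.044, OR 1.04.
  - True OR 1.10, age OR 6: 0.095 − 1.792 × 0.10 = −0.084, OR 0.92.
  - True OR 1.00, age OR 4: −0.139, OR 0.87.
- d = −8: the multiplier is −20 / (225 + 16) = −0.083. True OR 1.20, age OR 4: 0.182 + 0.115 = 0.297, OR 1.35.
- d = 0: the multiplier is 0, so the approximation gives no confounding.

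**Simulation.** Logistic regression on 300,000 patients per scenario, with standard errors rescaled to n = 209. Power is by normal approximation at two-sided 0.05, counting rejections in the direction of the estimate.

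| True OR | d (bpm) | Age OR | Crude OR | Age-adjusted OR | Power, crude / adjusted |
|---|---|---|---|---|---|
| 1.20 | 10 | 4 | 1.04 | 1.20 | 6% / 45% |
| 1.10 | 10 | 6 | 0.92 | 1.10 | not meaningful (sign reversed) |
| 1.00 | 10 | 4 | 0.88 | 1.00 | no true effect |
| 1.50 | 10 | 4 | 1.27 | 1.50 | 73% / 96% |
| 1.20 | 0 | 4 | 1.18 | 1.20 | 40% / 44% |
| 1.20 | −8 | 4 | 1.32 | 1.20 | 82% / 44% |

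The gap between 1.18 and 1.20 at d = 0 is not confounding; it is the usual shift in an odds ratio when a predictor of outcome is left out. In the last row the higher crude power comes from an inflated estimate.

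**Continuous age.** A second set of runs (2000 per scenario, n = 209) assumed age SD 18 years, SD of change 15 bpm and a true OR of 1.25 per 10 bpm.

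- With a rise smaller by 1 to 3 bpm per decade and log-odds of admission up 0.3 to 0.5 per decade, the crude OR was 1.03 to 1.19 (power 6% to 44%). The age-adjusted OR was 1.26 (power 59% to 65%).
- With no true effect (2 bpm and 0.4 per decade), the crude model rejected in 17% of runs with OR 0.91; the adjusted model rejected in 4.6%.
- At 2 bpm and 0.4, the crude OR was 1.05 with an SD of 12 bpm and 1.16 with 20 bpm.
- At 0.4 per decade, with no age effect on the rise, the crude OR was 1.22. With a rise larger by 2 bpm per decade it was 1.34.

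**The case against.** The strongest reply is that the missing age term is a silence. Data Analysis does not call the regressions univariable or unadjusted, and a full protocol or analysis plan that is not shown may list covariates. A reader might infer that the investigators have committed to unadjusted models; the text does not say so. What stands is narrower: the article does describe its models, it lists the terms of one without age, and every use it states for age is descriptive.

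A reader might also infer from the Background that age alters the acute rise. It does not say that. It concerns normal levels in healthy people, and the within-person contrast removes an additive effect on level from the absolute change. Nor do the documents say that older patients are admitted more often. Both links are assumptions here.

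Third, the aim is exploratory within a feasibility study, so a crude association is a legitimate summary if labelled as such. The table by disposition would show an age imbalance, although it would not correct for one. Participants must use a device, and owners are expected to be younger. That may narrow the age range and reduce any bias. These points limit the weight of the concern but do not remove it.

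**Conclusion.** The concern holds in a limited form. As written, no analysis of change against disposition accounts for age, although age and frailty are recorded. If age affects both the size of the change and admission, the crude estimate can be masked, reversed or exaggerated.

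It is tempting to conclude that the estimate will be pulled toward or below the null. The documents do not support that, because it requires age to act on the rise and on admission in opposite directions, and they give no figures on either. With no age effect on the rise the distortion is small (1.20 seen as 1.18, or 1.25 as 1.22). With effects in the same direction it is upward (1.20 seen as 1.32). Every magnitude rests on assumed inputs and is sensitive to the SD of heart-rate change. The primary feasibility outcome is unaffected. This is a worthwhile, inexpensive improvement to an exploratory secondary analysis; it does not invalidate the plan.

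**What to change.** In Data Analysis, state that each change-disposition association will be reported both crude and adjusted for age. Use continuous age if date of birth is kept. Otherwise use the age category, since the article says date of birth is used to compute a category and that the stored data hold no identifiers. Add the Clinical Frailty Scale where event numbers allow, and interpret the crude estimate as unadjusted.

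The cost is slightly more analysis and one or two extra model terms. Admissions to critical care may be too few to support them; if so, report that outcome crude and say why. No new data item is proposed. Medication use is named in the Background but is not among the data items, and the Results section shows that patients have already been included, so it cannot be added for this study.

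### Pearson's r is fixed for the exploratory correlations with no rank-based alternative, although the same section foresees non-normal data (minor)

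*Protocol article*

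**What the plan says.** All statements come from the Data Analysis section of the protocol article.

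- Normality: "All variables will be assessed for normality".
- Comparison of continuous data between groups: an unpaired t test when data are normal, otherwise "the Wilcoxon rank sum test (if the data are not normally distributed".
- Heart rate and step count at the different time points may be summarised by average or by median, so non-normal data are foreseen.
- Correlation, as a secondary exploratory analysis: "the correlation between potential outcomes will be tested using Pearson coefficient correlation analysis". No condition on the distribution and no rank-based or transformed alternative is given.
- Strength labels: "below 0.10 negligible, between 0.10 and 0.39 weakly correlated, between 0.40 and 0.69 moderately correlated", then "between 0.70 and 0.89 strongly correlated, and above 0.89 very strongly correlated". Neither the absolute value nor the sign of r is mentioned.

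The section does not list the pairs of variables to be correlated. Changes are to be expressed both as absolute and as percentage change from a home baseline.

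**The concern.** The plan checks for non-normality and acts on the result when groups are compared, but not when variables are correlated. That would matter little if the correlated variables were roughly symmetric. The study's physiological quantities include step counts and percentage changes in steps. A percentage change in steps cannot fall below -100%, has no upper limit, and becomes very large when the baseline count is low. Right skew and outlying values are therefore likely.

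Pearson's r is sensitive to both. Skew in one variable usually pulls it towards zero, while a single extreme patient can push it away from zero. Since the result is then turned into a verbal label by fixed cut-offs, the label can depend on the measurement scale or on one patient. The labels are also written for positive r only, so a negative coefficient has no clearly assigned word.

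**Working it through.** The article states no correlation, power or sample size for this analysis, so there is no figure to reproduce. The checks below show how far Pearson's r can move.

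**Inputs.** From the article: the method, the label bands, and 209 patients with data on at least two collection points (Results). Assumed: one normal variable X; one log-normal variable Y with log-SD s between 0.25 and 1.2; a latent correlation ρ between X and log Y. If Y is a ratio to baseline, its percentage change is 100 × (Y - 1). This is a linear rescaling and leaves r unchanged.

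**Effect of skew.** For this model:

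- Pearson r = ρ × s / √(exp(s²) - 1)
- Spearman = (6/π) × arcsin(ρ/2), whatever the value of s

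Example at s = 0.85: s² = 0.7225, exp(0.7225) = 2.060, √1.060 = 1.029, factor = 0.85/1.029 = 0.826.

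| log-SD s | share of ρ kept by Pearson | Pearson at ρ = -0.50 | Spearman at ρ = -0.50 |
|---|---|---|---|
| 0.25 | 0.984 | -0.492 | -0.483 |
| 0.5 | 0.938 | -0.469 | -0.483 |
| 0.85 | 0.826 | -0.413 | -0.483 |
| 1.0 | 0.763 | -0.381 | -0.483 |
| 1.2 | 0.669 | -0.334 | -0.483 |

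The loss is 2% to 6% at s = 0.25 to 0.5, and about 17% and 33% at s = 0.85 and 1.2. In 2,000 simulated samples of 209 at ρ = -0.50, mean Pearson r was -0.470 at s = 0.5 and -0.396 at s = 1.0, close to these values.

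**Effect on detection.** In 2,000 simulated samples of 209 at ρ = -0.30, the share with p < 0.05 was 0.989 (Pearson) and 0.987 (Spearman) at s = 0.5, and 0.945 and 0.992 at s = 1.0. The difference is nil at mild skew and small at marked skew.

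**Effect of one outlier.** Take 208 patients with two uncorrelated standard normal variables and one patient at (-6, 8). Approximately:

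- covariance = -48/209 = -0.230
- variances = (208 + 36)/209 = 1.167 and (208 + 64)/209 = 1.301
- r = -0.230 / √(1.167 × 1.301) = -0.186

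Simulation gave a mean Pearson r of -0.186 and a mean Spearman of -0.012. Under the plan's bands applied to size, one patient turns no correlation into a weak one.

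**Labels.** Applied to the absolute value, coefficients of -0.20, -0.50, -0.80 and -0.95 are weak, moderate, strong and very strong. Applied to the signed value as printed, all four fall in the lowest band.

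**The case against.** The strongest reply is that little rests on this analysis. It is labelled secondary and exploratory. The primary outcome is feasibility, and associations with clinical end points are assigned to linear and logistic regression. Normality is to be checked anyway, and an analyst who found skew might well switch to a rank coefficient. Pearson's r is also a legitimate measure of linear association, and at mild skew it differs hardly at all from the rank version. All of this stands and limits the point to a minor one. It does not remove it: the article names the method and leaves out the safeguard that it gives for group comparisons.

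A reader might go further and infer that an expected inverse link between heart rate and steps will be shrunk and then called negligible. The documents do not support that:

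- They name no heart rate and step pair, predict no direction and give no distribution for steps.
- Shrinkage is not certain, since outliers can inflate r.
- A change of label depends on where the true value lies. At ρ = -0.60, Pearson is -0.60 × 0.826 = -0.50 at s = 0.85 and -0.60 × 0.669 = -0.40 at s = 1.2, still moderate. At ρ = -0.30 both coefficients are weak. A value of -0.50 is vulnerable because it lies not far above the 0.40 cut-off.
- The bands grade strength, and an analyst would ordinarily read them as size. The missing absolute value is a wording defect, not a plan to report strong negative correlations as negligible.

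**Conclusion.** The point holds as a minor one. Pearson's r is prescribed for all exploratory correlations whatever the distribution, which does not match the section's own treatment of non-normal data in group comparisons. Under the assumed model the coefficient keeps about 94% of the latent correlation at a log-SD of 0.5, 83% at 0.85 and 67% at 1.2, and one outlying patient in 209 can create an apparent r of about -0.19. The direction of distortion is therefore open.

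These sizes rest on assumed log-normal skew and an assumed outlier. The figure of 209 counts patients with at least two collection points, so the number with both variables of any given pair may be smaller. The inconsistency itself, and the absence of the absolute value from the labels, can be read from the text without any assumption. No primary or named secondary end point is affected.

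**What to change.** In the Data Analysis section:

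1. Use Spearman's rank correlation with a 95% confidence interval, or Pearson's r on log ratios, for any pair involving step counts or percentage change. At the least, do so wherever the planned normality check fails.
2. State that the strength labels apply to the absolute value of the coefficient and that the sign is reported with it.

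The cost is two phrases. No new data are needed, and the loss from Spearman's coefficient when data are in fact close to normal is negligible (power 0.987 against 0.989 in the mild-skew simulation).

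### The secondary end points and one baseline rule need data from 1 month before presentation, but the listed data items stop at 1 week, and a second baseline rule has no fixed day

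*Protocol article*

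**What the plan says.** **What is to be analysed.** In the Protocol article, the secondary study end points (Textbox 2) include "The difference between the heart rate at rest from the wearable device 24 hours, 1 week, and 1 month before assessment by emergency practitioners", set against the initial vital signs on admission, and "The change in daily steps taken in the month before admission to acute care". Secondary Outcome Measures repeats the three heart-rate look-backs, "24 hours, 1 week, and 1 month before clinical assessment from the wearable device". The Abstract promises trends over the preceding month, and Sample Size Calculation says that the sample should serve the 24-hour, 1-week and 1-month comparisons.

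**What is to be recorded.** The data-item list under Study Procedures (Textbox 3) takes device heart rate "on three-time points, namely on presentation, within 24 hours before presentation and within 1 week (plus or minus 1 day) before presentation". For steps: "The daily walking distance of the 7 days before the presentation will be recorded". No listed item reaches further back.

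**What counts as baseline.** Data Analysis gives two rules. Changes between measurements are described as "percentage change from the first measurement taken at home before admission as the assumed baseline". Later, at the end of the paragraph on exploratory analyses, the percentile change (which I read as percentage change) in heart rate and steps is taken from a "baseline, which will be assumed to be at 30 days before a hospital visit". The section also says that missing data will not be imputed.

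**The concern.** Two things do not fit together.

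First, the analysis needs values that the data list does not provide. An analysis plan cannot repair this later: if the 1-month values were not recorded, there is nothing to analyse.

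Second, the two baseline rules agree only if the earliest home value is the day −30 value. If nothing older than a week was recorded, the only usable rule is the one with no fixed day.

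At stake is the meaning of change. The objectives in Textbox 1 ask how far patients have moved from values recorded while they were stable and well. Anticipated Findings itself expects vital signs to shift in the days or hours before presentation, which is the period that the listed items cover. A reference value from that period may already carry part of the illness. The same changes also enter the planned regressions on admission, critical care and discharge.

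**Working it through.** No power or precision formula applies. The only planning figure, 40 hospitals × 50 patients = 2000 screened, reproduces as a product and has no bearing here. The check sets the required look-backs beside the recorded ones.

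| Quantity | Required | Recorded (Textbox 3) | Shortfall |
|---|---|---|---|
| Heart rate, 24 hours | yes | yes | none |
| Heart rate, 1 week | yes | yes, ± 1 day | none |
| Heart rate, 1 month | yes | no | see step 1 |
| Daily steps | month before admission | 7 days | see step 2 |
| Baseline at day −30 | yes | no | see steps 1 and 2 |

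**Step 1, heart rate.** The 1-week point with its tolerance spans days −6 to −8. Distance to day −30: 30 − 8 = 22 days at best, 30 − 6 = 24 days at worst. If the 1-week item is instead read as any time in that week, the earliest value is still about day −8. Of the three look-backs in the end point, 2 are supported and 1 is not.

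**Step 2, steps.** The earliest recorded day is day −7. Distance to day −30: 30 − 7 = 23 days. Share of a 30-day window recorded: 7/30 = 23%.

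**Step 3, the 30-day baseline.** By steps 1 and 2, no listed heart-rate or step item supplies it.

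**Step 4, the first-home-measurement baseline.** From the listed items, the earliest home heart rate is the 1-week value where that exists and the 24-hour value where it does not. The Results section says how often series are incomplete: of 452 included patients, 209 had data on at least 2 collection points, so 209/452 = 46%, and 452 − 209 = 243 (54%) did not. The article does not say which points the 209 had. Two points could be presentation with 24 hours, presentation with 1 week, or 24 hours with 1 week. Under this rule, with no imputation, patients in the same summary could be referenced to different lags. The number so affected cannot be worked out from the article.

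**The case against.** **A condensed article.** The case report form and the investigators' device guide are not shown, and either may reach back a month. This is a fair limit: the statement that stands is that the quantities cannot be computed from the listed items. A reader might infer that 1-month data are missing for every patient, but the article cannot establish that. It remains a contradiction and not mere brevity, because the list gives a count of time points, their windows and a tolerance.

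**One baseline, loosely worded.** If a month of data was intended, the earliest home value is the 1-month value and the two baseline sentences describe one rule. That is a reasonable reading, but it depends on day −30 data that the list does not contain.

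**A fallback rule.** A reader might infer that the first-home-measurement rule was written to replace a missing 30-day value. No section says so. It is simply the only one of the two rules that the listed items can support.

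**Pooling of lags.** A reader might conclude that the change results as a whole are uninterpretable. The end points and outcome measures plan a separate contrast at each look-back, and the 24-hour and 1-week contrasts are supported. Lags can mix only under the one sentence on the first home measurement. The 1-week contrast is also useful in itself: Anticipated Findings treats stability over the preceding week as a use case.

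**Size of any bias.** It is tempting to put a figure in beats per minute on the understatement. The documents give neither the rise from the well state nor the share of it present a week or a day earlier, so any such figure would only restate an assumption.

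**Conclusion.** The point holds as an internal contradiction. As the data items are listed, one of three heart-rate contrasts, the month-long step change and the 30-day baseline cannot be delivered. The shortfall is 22 to 24 days for heart rate and 23 days for steps. The second baseline rule has no fixed day and could, with incomplete series, refer different patients to different lags.

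The direction of any effect on the results is conditional. If heart rate or steps had already moved towards the presentation value by the reference day, the change from the well state is understated. Its size is unknown.

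A reader might infer that the study's main result is undermined. It is not: device use, recruitment and retention do not depend on these look-backs. The fault is confined to secondary end points in a self-described feasibility study. It still needs correcting, because stated end points cannot be produced as written and the choice of baseline alters every percentage change reported.

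**What to change.** Establish what the case report form captured, then make all the sections agree.

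- **If it captured 1-month data:** correct the data-item list to show the day −30 heart rate and the month of daily steps. Use day −30, with a stated tolerance, as the only baseline, and remove the first-home-measurement wording. The cost is a correction to the list and to Data Analysis.
- **If it did not:** delete the 1-month end points and the 30-day baseline from the Abstract, Textbox 2, Sample Size Calculation, Data Analysis and Secondary Outcome Measures. Set the heart-rate baseline to the 1-week value (± 1 day) and limit the step change to the 7 recorded days. Report the 24-hour contrast separately, with no substitution of one lag for another. Describe the baseline as one week before presentation, not as the stable and well state, since a value that recent may already reflect the illness. The cost is wording and a narrower claim: the 1-month heart-rate contrast and the month-long step trend are given up.

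Going back to collect the missing values does not look open for this cohort. Results reports that the main study ran in May 2024, and Handling and Storage of Data and Documents says that the data hold no patient identifiers.
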